***Outcome measures***

These will be assessed via self-reports at 33 months (age 15/16). All of our outcome measures have been piloted successfully in our pilot RCT and other studies (ordinal alphas for multi-item scales reported below).(42, 53)

Our primary outcome will be a binary measure of non-competent first sex. This measure has been chosen because it: provides the best measure of overall sexual health in this age-group regardless of gender or sexual orientation; is strongly associated with multiple adverse sexual health outcomes including STIs, non-volitional sex, unplanned pregnancy and sexual dysfunction;(1) was recommended through PPI with policy stakeholders and young people; is appropriate given the intervention now includes DRV prevention; and is sufficiently prevalent among trial participants to provide statistical power through a pragmatic sample size.(1, 2) It has been recommended as an impact measure by the World Health Organisation, is sensitive to intervention effects and is starting to be used in evaluations.(69, 70) Non-competent first sex will be assessed among trial participants having sex for the first time between baseline and follow-up, using the established Natsal self-report measure defined in terms of the absence at first sex of: autonomy of decision; equal willingness of partners; its being the ‘right time’; and, for those reporting heterosexual intercourse, use of effective contraception.(1, 2) We will assess non-competent first sex for those reporting only same-sex intercourse via the other items but not assessing protection because this is primarily relevant for anal sex, which is extremely rare among this age group and according to our PPI is unacceptable to include in school surveys.(71) This primary outcome replaces pregnancy, which was the indicative primary outcome in the pilot RCT, because: pregnancy was judged too narrow a measure of sexual health; pregnancy is relevant only for girls and heterosexual sex; pregnancy does not reflect the areas of greatest sexual health need in terms of current trends; and powering a trial on this outcome would require an unfeasibly large school sample of >100 schools per arm.(46) Non-competence at first sex strongly predicts a range of subsequent adverse sexual health outcomes listed above, more so than is the case for other measures of early sexual-risk behaviour.(1, 2) The pilot RCT indicated good performance of the Natsal competence measure in terms of completion (88%) and inter-item reliability (ordinal alpha=0.74).

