
Secondary outcomes will examine other important potential benefits:

- age at sexual debut, using an adapted version of the RIPPLE measure;(72)
- non-use of contraception at first and last sex among those reporting heterosexual intercourse, using an adapted version of the RIPPLE measure;(72)
- number of sexual partners, using an adapted RIPPLE measure;(72)
- dating and relationship violence (DRV) victimisation (including non-volitional sex) measured using an adapted version of the short Conflicts in Adolescent Dating Relationships Inventory (sCADRI) scale which is widely used and was piloted for reliability in our recent Project Respect study (ordinal alpha=0.89);(42, 73, 74)
- sexually transmitted infections (STIs), focused on self-reported diagnosis with common infections, using an adapted version of the RIPPLE measure;(72)
- pregnancy and unintended pregnancy for girls and initiation of pregnancy for boys using adapted versions of the RIPPLE measures.(72)

*Intermediate outcome measures:* We will not undertake mediation analysis because this requires two waves of follow-up, which is not planned in the interests of minimising costs and maximising school retention. It is our experience across studies that multiple follow-ups reduce rather than maintain school engagement and hence response rates.(52) However, informed by our theory of change,(64, 65) we will undertake exploratory analyses of intervention effects on the following ‘intermediate’ outcomes(75) using existing measures(36, 39, 51, 76) tested for reliability in our pilot (ordinal alphas indicated below for multi-item scales): school-level social norms supportive of healthy relationships and sexual health (alpha=0.77); individual-level attitudes towards DRV (alpha=0.65) and gender roles (alpha=0.68); individual-level school engagement (alpha=0.74); career/educational aspirations; sexual health knowledge (alpha=0.78); sexual health and contraceptive skills (alpha=0.92); sexual communication self-efficacy (alpha=0.93); and communication with parents; sexual and reproductive health services access (alpha=0.83) DRV perpetration (including non-volitional sex) measured using sCADRI (ordinal alpha=0.88); and sexual harassment.(77)

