A statistical analysis plan will be drafted by the CTU and a data dictionary by the fieldwork team. Statistical analysis of survey data will be led by the CTU, with analysis of fidelity data by the fieldwork team and economic data by [name]. School randomisation and retention, and student response rates will be described using a CONSORT diagram.(88) Baseline and follow-up data will be tabulated by arm. Continuous outcomes will be summarised for each trial arm using means and standard deviations and binary outcomes will be summarised for each trial arm using numbers and percentages. We will conduct intention-to-treat analyses of primary and secondary outcomes (88) as well as exploratory analyses of our intermediate outcomes (RQ1) to estimate intervention effects, reporting 95% confidence intervals and P values for primary and secondary outcomes but not for exploratory analyses of the intermediate outcome. The analytic sample will be students providing follow-up data at 33 months. Analyses will account for school clustering. All outcomes will be analysed using generalised estimating questions (GEEs) with an exchangeable correlation structure and the sandwich estimator of variance to adjust for clustering, with small sample bias correction for the degrees of freedom. For binary outcomes GEEs will be fitted, with a log link to estimate risk ratios and identity link to obtain risk differences. In the event of low prevalence resulting in non-convergence of the GEE model a hierarchical modified Poisson regression model will be used to obtain risk ratios, followed by marginal standardisation to obtain risks for calculating risk differences where required. For continuous outcomes GEEs with an identity link will be used to obtain mean differences.

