The primary analysis of all outcomes will include adjustment for stratification factors used in the randomisation. Our primary analysis will be an analysis that is adjusted for the stratification factors only. An additional adjusted analysis will be carried out which will adjust for prespecified cluster level summaries of baseline student age, gender, ethnicity and SES (as measured by the family affluence scale), imputed where feasible from baseline data if missing at follow-up. In addition, any other major imbalances observed between randomised groups will be adjusted for in exploratory secondary analyses. Interim analyses will not be conducted and will not inform intervention modification or discontinuation because this is a cluster RCT with one follow-up wave.

We will undertake exploratory tests of interaction to assess how effects are moderated, including by student gender, sexual orientation, ethnicity and SES as well as by school GCSE attainment and local deprivation (RQ2). These will be exploratory, with limited statistical power. We will also undertake complier-average causal effects analyses to examine how effects are affected by fidelity of implementation (RQ3). Economic analyses will calculate intervention costs and cost-effectiveness (RQ4) (see below). Descriptive statistics will describe fidelity, reach and acceptability using Chi-square tests to examine differences between schools. These will examine whether fidelity differs by school-level GCSE attainment and local deprivation, and whether student-level reach and acceptability differ by student-level gender, sexual orientation, ethnicity and SES. (RQ5). Quantitative and qualitative data from control schools will be analysed to describe usual treatment in control schools (RQ6). Qualitative data will also be used to develop hypotheses about implementation processes/intervention mechanisms and how these might vary between schools or students (RQ7). We will draw on all data to refine the intervention theory of change and draw conclusions about the potential for the intervention to be delivered and be effective elsewhere (RQ8).

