***Economic analyses:*** The aim is to evaluate the cost-effectiveness of Positive Choices versus the comparator from a health and social care perspective as preferred by NICE, additionally considering education and voluntary-sector perspectives.(89) An economic analysis plan will be drafted before receipt of the final data. For our primary cost-utility analysis, costs and CHU-9D data will be combined to present mean cost and quality-adjusted life-years and incremental cost-effectiveness ratios. A secondary cost-consequences analysis will additionally be undertaken for the other trial outcomes as recommended by NICE public health methods guidance(90) because there may not be a strong correlation between CHU-9D and these other outcomes. We will use a multi-level modelling approach with random intercepts to estimate the mean and standard errors for both cost and effects along with the covariance matrix.(91) From these, mean incremental net benefit and confidence intervals will then be estimated. Missing data will be handled using multiple imputation.(92) The time horizon will capture costs and outcomes within the trial. The pilot RCT indicated these analyses as feasible.

***Qualitative data*** will be subject to thematic content analysis (in vivo/axial codes; constant comparison(93)) informed by realist approaches to evaluation(85) and May’s implementation theory(83) to: examine implementation processes, potential intervention mechanisms and how these vary between schools and students. Realist analyses of qualitative data will inform refinements to our theory of change and, where possible, inform additional hypotheses about how context interacts with intervention mechanisms to generate outcomes. These analyses and hypotheses will be posted online prior to assessing them via post hoc exploratory mediation and moderation analyses of quantitative data. In the light of these analyses, we will refine our intervention theory of change, defining what contextual factors promote or impede implementation and mechanisms. This refined theory of change will be the means by which we will make evidence-informed suggestions about the potential for the intervention to be delivered effectively elsewhere.

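### The plan rules out mediation analysis for want of a second follow-up wave but later schedules it, and it omits confidence intervals for the intermediate outcomes offered in its place

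*Combined protocol and SAP*

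**What the plan says.** Three statements in the combined protocol and SAP bear on this.

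- **Outcome measures, intermediate outcomes:** "We will not undertake mediation analysis because this requires two waves of follow-up, which is not planned". What the plan offers instead is that "we will undertake exploratory analyses of intervention effects on the following" intermediate outcomes.
- **Data management and analysis, paragraph on qualitative data:** hypotheses suggested by the realist qualitative work will be "posted online prior to assessing them via post hoc exploratory mediation and moderation analyses of quantitative data". The use made of the results is stated: "In the light of these analyses, we will refine our intervention theory of change". The refined theory is then the basis for suggestions about delivering the intervention elsewhere, which is RQ8.
- **Data management and analysis, statistical methods:** effects will be estimated "reporting 95% confidence intervals and P values for primary and secondary outcomes but not for exploratory analyses of the intermediate outcome".

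The same section, explaining why there are no interim analyses, says that "this is a cluster RCT with one follow-up wave". Minimising bias adds that the post hoc hypotheses will be few and made public before they are tested.

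**The concern.** A reader cannot tell whether mediation will be done. If it is, the plan has already given the reason why its data cannot support it.

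Timing makes this worse for the primary outcome: "Non-competent first sex will be assessed among trial participants having sex for the first time between baseline and follow-up". The event therefore lies before the 33-month survey. Sexual health knowledge, communication self-efficacy, talk with parents and use of services, all recorded at that survey, may have changed because a student had first sex. A mediation model would read that association in the opposite direction.

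The second issue is separate. The effects on intermediate outcomes are what the plan puts in place of mediation. Without intervals, a reader cannot tell a precise null from an uninformative estimate. Mechanisms are a stated aim of the trial (Rationale and aims), so both issues feed a conclusion that the trial intends to draw.

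**Working it through.** The plan states no figure on this point, so the main check sets the passages side by side. The arithmetic is illustrative.

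**1. Do the two statements conflict?** Outcome measures gives a reason for excluding mediation: two follow-up waves are needed. Data management and analysis confirms one. That reason concerns the design, so it covers any mediation analysis, whether or not it is labelled exploratory. Publishing hypotheses first limits data dredging but does not create temporal order. The conflict stands.

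**2. Order of mediator and outcome.** Students are surveyed at baseline, before randomisation, and at 33 months (Assessment and follow up). A mediator taken from the student survey after the intervention can only come from the second survey. First sex that counts towards the primary outcome occurs before it, by definition. The lag depends on the shape of incidence, which the documents do not give:

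- uniform over 33 months (assumption): mean lag = 33/2 = 16.5 months;
- rising linearly from zero (assumption): mean debut at (2/3) × 33 = 22 months, so mean lag = 33 − 22 = 11 months.

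The ordering does not depend on these shapes, and the lag is not a measure of bias.

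**3. Can one-wave data produce a false mediated effect?** Inputs from the plan: control risk 9% and intervention risk 5.85% (risk ratio 5.85/9 = 0.65), in 46 schools of 140 students. Assumed: the intervention raises the mediator by 0.2 SD, and the mediator has no true effect on the outcome. The indirect effect is a × b, where a is the arm difference in the mediator and b is the slope of outcome on mediator, adjusted for arm. School clustering was not simulated. Means over 300 simulated trials:

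| Assumed structure | Indirect effect | Total effect | Share apparently mediated |
| --- | --- | --- | --- |
| No feedback, no shared cause | 0.00004 | −0.0312 | about 0% |
| Outcome lowers later mediator by 0.3 SD | −0.00424 | −0.0313 | 13.5% |
| Shared unmeasured cause only (−0.3 SD on mediator, 0.3 on log risk) | −0.00122 | −0.0315 | 3.9% |
| Both | −0.00514 | −0.0317 | 16.2% |

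The second row can be checked by hand.

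- Mean within-arm variance of the outcome = (0.09 × 0.91 + 0.0585 × 0.9415)/2 = 0.0685.
- b = −0.3 × 0.0685 / (1 + 0.09 × 0.0685) = −0.0204.
- a = 0.2 + 0.3 × 0.0315 = 0.2095.
- a × b = −0.0043, and −0.0043/−0.0315 is about 14%.

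**4. The reporting rule.** Outcome measures lists 12 intermediate outcomes: social norms; attitudes to DRV; attitudes to gender roles; school engagement; aspirations; knowledge; skills; communication self-efficacy; communication with parents; service access; DRV perpetration; sexual harassment. Read literally, the rule withholds both the interval and the P value for each.

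The arm-level means and SDs, or counts, that the plan will tabulate allow only a precision that ignores clustering. If the plan's ICC of 0.015 for the primary outcome also held for these outcomes (an assumption), then with 140 students per school the design effect is 1 + 139 × 0.015 = 3.085. An interval derived that way would be too narrow by a factor of √3.085 = 1.76.

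**The case against.** The strongest reply has four parts.

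- **The mediators are not named.** The qualitative-data paragraph does not say that they will be the 33-month intermediate outcomes, nor that the outcome will be first sex. Logbooks and observations come from delivery in 2022–24, before the final survey, and some outcomes, such as contraception at last sex, are not fixed at debut. This stands. The reverse-order argument is therefore conditional on survey-measured mediators and first sex as the outcome. It does not remove the conflict, because Outcome measures makes no exception for other mediators or outcomes.
- **The work is exploratory and guarded.** Hypotheses are few and made public beforehand. This is a real protection against selective testing, but not against reverse causation.
- **Mechanism conclusions have other support.** A reader might infer that all the trial's conclusions on mechanism would be unsound, or that bare point estimates are the only evidence for them. The documents do not support that. RQ7 rests on qualitative data from all intervention schools with four case studies, RQ8 draws on all data, and moderation needs no second wave.
- **The interval rule is a reporting matter.** It covers intervention effects on intermediate outcomes and does not say how mediation estimates would be presented. Omitting P values from exploratory analyses is defensible. The SAP agreed in January 2023 is not reproduced as a separate text, so its reporting tables cannot be checked, although the version history says that the protocol was aligned with it. These points stand, but omitting intervals remains a weakness.

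**Conclusion.** The point holds in a limited form. The two sections contradict each other on mediation and must be reconciled. Mediated effects estimated from 33-month intermediate outcomes, with first sex as the outcome, would be open to reverse causation. The size of the bias cannot be known from the documents: the range of about 0% to 16% rests wholly on assumed feedback and confounding, and shows only that a false indirect effect can arise where none exists. The missing intervals affect 12 exploratory estimates.

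The estimates for the primary and secondary outcomes are untouched. This is a change that should be made to protect the interpretation of RQ8; it does not threaten the trial's main result.

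**What to change.** - **Mediation.** In the qualitative-data paragraph of Data management and analysis, delete the words *mediation and*. Test the published hypotheses by moderation and by intervention effects on the intermediate outcomes. If the team prefers to keep mediation, amend Outcome measures to say so, and state the estimand, the mediators and outcomes concerned, the temporal-order and confounding assumptions, the sensitivity analyses and the limits on interpretation.
- **Intervals.** In the statistical methods of the same section, report 95% confidence intervals without P values for the intermediate outcomes, labelled exploratory.

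The preferred route needs two wording changes and no new data, since the GEE models specified for all outcomes already produce the intervals. The price is that there will be no quantitative mediation result, which Outcome measures already accepts.

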***Minimising bias***

To maximise external validity, the study will aim to recruit a broadly representative sample of secondary schools in central and southern England. To maintain the integrity of the intervention and analyses, the fieldwork, intervention and CTU teams will be separately managed. To minimise confounding and bias, the evaluation design will be experimental with random allocation of schools not individual students (to minimise contamination and preserve the school-level theory of change) stratified by school-level GCSE attainment and local index of deprivation by the CTU after baseline surveys. To minimise retention bias, we will maximise school retention using the methods described above, including school payments. To minimise analytic bias, we will publish a study protocol including analytic plans which clearly distinguish between primary, secondary and exploratory analyses. Furthermore, quantitative data will be collected and analysed blind to allocation (blinding of participants is not possible) with primary analyses being intention-to-treat focused on valid and reliable outcome measures adjusting for potential baseline imbalances. Our analytical sample will be those students providing data at follow-up with imputation of missing baseline data on socio-demographic factors and age of sexual debut based on responses at follow-up. Quantitative analyses will be undertaken by statisticians from LSHTM’s accredited CTU staff, with oversight by the DMEC. To minimally bias thematic analysis, qualitative analyses will be undertaken prior to quantitative analyses. To minimise ‘data dredging’ within exploratory analyses, we will ensure these focus on a small number of post hoc hypotheses that have been developed informed by our qualitative analyses and posted online prior to quantitative assessment.

**Public and policy involvement**

The phase-III study will continue to collaborate with the ALPHA and policy-practice stakeholder groups. These are discussed above, integrated into our description of methods. Meetings with each of these groups near the start of the study will critically appraise drafts of the new intervention materials prior to their finalisation. A meeting with each of these groups near the end will focus on interpretation and dissemination of our results and the potential for scale-up of the intervention. We include letters of support from organisations indicating that they are already willing to participate in this group. We will also invite a teacher and two students from schools in the pilot RCT to sit on the SSC so that this takes on a broader perspective.

**Ethical issues, safeguarding and SAEs**

Ethical approval for the study will be obtained from the LSHTM Ethics Committee. Any member of the research/fieldwork team working with students without supervision by school staff will be required to have a full disclosure and barring services check. All work will be carried out in accordance with guidelines laid down by the Economic and Social Research Council, the Data Protection Act 1998, and GDPR.

Head teachers as gatekeepers will be asked for informed consent for intervention and random allocation by the principal investigator. Parents will have a statutory right to withdraw their children from sex education lessons in intervention and control schools. In terms of research participation, as is normal within public-health and educational research in secondary schools in the UK (e.g. RIPPLE trial), informed written opt-in consent will be sought from all research participants by trained fieldworkers, including students judged by teachers as competent to provide this. Parents will also be given the right to opt out their children if they wish. In all cases of data collection, participants (and, in the case of students, their parents also) will be given an information sheet one week before data collection and will be able to opt out (or, in the case of parents, can opt their children out) of this should they wish. Just before data collection, participants who have not previously opted or been opted out will receive an oral and written description of the study and the chance to ask questions of trained fieldworkers. In the eventuality of online surveys being conducted in schools not allowing face-to-face fieldwork, participants will receive the same information and have the same opportunity to ask questions of trained fieldworkers via telephone or internet technologies in real time. Participants will then be advised that participation is voluntary and they may withdraw at any point. All participants will be advised that they are free to withhold consent and this will not be communicated to others within the school or family. Students will then be asked for their written consent to participate by the fieldworker. In the eventuality of online surveys being conducted, students will be asked to consent via preliminary pages of the online survey. Students opting not to participate in research activities will continue with normal school activities.

All participants will be informed in consent materials that the information they provide will be treated with anonymity and confidentiality, as well as the circumstances in which we would need to breach confidentiality. We will maintain standard operating procedures for dealing with safeguarding concerns. In the pilot, we worked with a child protection social worker to develop a priori categories of abuse reported through the research that would necessitate our breaching confidentiality to ensure individuals are offered care and protection. These are informed by existing clinical guidelines and for example include sex before age 13 as well as forced sex or other serious abuse. These categories balance our ethical duty of promoting participant autonomy and wellbeing. Where defined categories of abuse are indicated in questionnaires, we will contact the safeguarding lead in the school. Where these are reported directly to research staff during data collection, we will first discuss the need for a response with the individual prior to contacting the school safeguarding lead. In each school and within NCB, a senior member of staff will be identified who is not directly involved with the intervention and to whom staff or students may go if they have complaints about any elements of the intervention or research.

Interviews, focus groups and observations will not aim to explore experiences of sex or abuse. In the case of focus groups, our researchers will be trained to ensure that discussions do not move in the direction of personal disclosures since this is not the purpose of the groups and it would be very difficult to ensure that other participants do not communicate such disclosures outside the group. However, if participants in interviews or focus groups describe abuse or become upset in any way, our researchers will be trained in how to respond. In interviews, researchers will stop the interview and determine need for a referral to support within the school. In focus groups, researchers will aim to stop sensitive discussions, and assess need for individual support at the end or stop the focus group if the assessment is that immediate support is needed.

We will monitor safeguarding concerns and standard categories of SAEs via regular consultation with schools. The SSC, data monitoring and ethics committee and LSHTM Ethics Committee will be provided with anonymised reports of safeguarding concerns and SAEs, categorised by type, circumstances and the plausibility that these are related to intervention or research activities. Because all follow-ups occur at 33 months there will be no interim analyses. The DMEC will consider stopping if there is any suggestion of an association between the number of safeguarding concerns and SAEs plausibly associated with the intervention or trial and the arm of the trial.

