**Data Monitoring and Ethics Committee**

The DMECs main role is as follows:

- It is the only body involved in a trial that has access to the unblinded comparative data.
- The role of its members is to monitor these data and make recommendations to the TSC/SSC on whether there are any ethical or safety reasons why the trial should not continue.
- The safety, rights and well-being of the trial participants are paramount
- The DMEC considers the need for any interim analysis advising the SSC regarding the release of data and/or information.
- The DMEC may be asked by the SSC, Project Sponsor (LSHTM) or Project Funder (NIHR) to consider data emerging from other related studies.
- There are also rare occasions when the DMEC chair might be asked, through the chair of the SSC ([name], City University), by the Project Funder (NIHR) to provide advice based on a confidential interim or futility analysis if serious concerns are raised about the viability of the study or if the research team are requesting significant extensions.
- Criteria should be agreed at which continuation of the trial is considered futile and the DMEC would only indicate if these had been passed or not as this would limit the potential for un-blinding.

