***Comparator and potential contamination:*** We will examine RSE and sexual and reproductive health services provision in and around control schools in order to describe usual treatment. We will examine the potential for contamination across arms to assess whether this is a threat to internal validity. Data will be collected via: student surveys; and structured phone interview with 1 staff-member (using the School Health Research Network school health questionnaire(87)) per control school per year.

***Implementation processes/intervention mechanisms and context:*** Informed by May’s implementation theory and realist evaluation,(83, 85) we will collect qualitative data and analyse these in order to explore implementation processes and intervention mechanisms (beneficial or harmful) and how these vary between schools and students. Data will be collected from all intervention schools via: phone interview with one staff-member and face-to-face focus group with 4-8 students per school (purposive by involvement and gender) per year of delivery. More in-depth data will be collected from 4 case-study schools purposively sampled by GCSE attainment and local deprivation via: phone interview with 4 staff-members and 2 face-to-face focus groups with 4-8 students (purposive by involvement and gender and ethnicity) per year of delivery. It will not be feasible in schools to purposively sample students by sexual orientation or socio-economic status but we will strive to be inclusive of a diversity of students.

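### The stated DMEC safety comparison counts only events judged plausibly related, so it can tilt by arm without excess harm and omits unattributed excess; an all-event table by arm should be specified

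*Combined protocol and SAP*

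**What the plan says.** The section *Ethical issues, safeguarding and SAEs* sets out three steps.

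- **Collection** has no relatedness filter: "We will monitor safeguarding concerns and standard categories of SAEs via regular consultation with schools".
- **Reporting** to the SSC, the DMEC and the ethics committee is anonymised, with events "categorised by type, circumstances and the plausibility that these are related to intervention or research activities". Relatedness is a category here, not a condition for being reported. Arm is not among the listed categories.
- **The trigger**: "The DMEC will consider stopping if there is any suggestion of an association". The two quantities to be associated are given in the rest of that sentence: "association between the number of safeguarding concerns and SAEs plausibly associated with the intervention or trial and the arm of the trial". No test, count or level is attached.

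The earlier section on the DMEC's role is broader. On data by arm it says "It is the only body involved in a trial that has access to the unblinded comparative data", and the members are to advise "whether there are any ethical or safety reasons why the trial should not continue".

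The documents do not say who judges plausibility, or whether that person knows the arm. They specify no comparison of all events by arm.

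**The concern.** Randomisation makes the arms comparable for all events that occur in them. It does not make them comparable for a subset chosen by a judgement that depends on the arm. Whether an event is plausibly related to the programme is such a judgement, because outside the intervention arm there is no programme to relate it to.

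Two errors can follow. The trigger may be met through attribution alone, prompting a discussion about stopping when total events are balanced. Or a real rise in safeguarding concerns or SAEs in intervention schools may not count towards the trigger, because nobody linked those events to the lessons or campaigns. The second matters more. The outcome survey comes only at 33 months and there is no interim analysis, so school-reported events are the main information comparable by arm while the programme is being delivered.

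**Working it through.** The plan gives no event rate, safety threshold or safety power, so there is no figure to reproduce. The point rests on setting the passages side by side.

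**Step 1: what each arm can contribute.** *Intervention and comparator* says control schools continue their existing provision.

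| Type of event | Intervention schools | Control schools |
|---|---|---|
| Plausibly related to research activities | can count | can count |
| Plausibly related to the intervention | can count | cannot count, barring contamination |
| Not judged related to either | left out | left out |

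The second row tilts the count. The third row is where unattributed excess is lost.

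**Step 2: who supplies the events.** They come from consultation with schools. *Recruitment and randomisation* has the fieldwork team tell schools their allocation, so an intervention school knows there is a programme to which an event might be linked.

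**Step 3: routes of detection.** *Process evaluation data collection* plans, in every intervention school and each year of delivery, a "phone interview with one staff-member and face-to-face focus group with 4-8 students per school". Control schools have a "structured phone interview with 1 staff-member" per year. Student surveys are listed for control schools too, and the baseline and 33-month surveys are described without a difference by arm. Some routes are therefore shared and some are not.

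**Step 4: direction of the effect, with assumed counts.** None of these counts comes from the documents. Let *B* be background events per arm, *r* research-related events per arm, and *a* the share of intervention-arm background events judged programme-related, with no true harm.

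- All-event ratio, intervention to control: 1.0.
- Filtered expected ratio: (*r* + *aB*)/*r*.
- Low end, *B* = 20, *r* = 5, *a* = 0.05: (5 + 1)/5 = 1.2.
- High end, *B* = 50, *r* = 2, *a* = 0.20: (2 + 10)/2 = 6.0.

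Now suppose a true doubling of all events, 40 v 20.

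- If none of the 20 excess events is recognised as related, the filtered counts are *r* v *r*, a ratio of 1.0.
- If a quarter is recognised, they are *r* + 5 v *r*: 7 v 2 for *r* = 2, or 10 v 5 for *r* = 5.
- With Poisson counts and a nominal one-sided exact comparison at 0.05, the all-event table signals with probability 0.80. The filtered count signals with probability 0.01 to 0.37 across recognised shares of 0% to 25% and *r* of 2 to 5.

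These probabilities ignore clustering by school, and the plan specifies no such test. They show the direction only and are not an estimate for this trial.

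**Step 5: the qualifier.** In the trigger sentence, the phrase about plausible association may govern both safeguarding concerns and SAEs, or SAEs alone. On the second reading all safeguarding concerns count and the filter affects SAEs only. The text does not settle it.

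**The case against.** The strongest reply is that the trigger is a low-threshold prompt to deliberate, not a test. A false alarm costs a discussion. Committee members who see type, circumstances and relatedness will understand why programme-related events arise where the programme runs. The chair also agrees the content of the DMEC report in advance. This stands, and it limits the harm. It does not supply a comparison that randomisation supports, and the plan names none.

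Three stronger readings are tempting, and the documents do not support them.

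- **A reader might infer that unattributed harms are hidden from the DMEC.** They are not. Relatedness is a reporting category, and the committee has data by arm and a remit over any ethical or safety reason.
- **A reader might infer that the control count is zero by construction.** It is not. The trigger also admits events related to the trial, and research-related events can occur in both arms. Testing programme-attributed events against zero would not describe the stated trigger.
- **A reader might infer that events are sought harder in intervention schools.** The consultation with schools is not said to differ by arm. Control schools also have student surveys, questionnaires are a named route by which abuse is identified, and focus groups are to be steered away from personal disclosures. Extra process-evaluation contact is a reason to record how each event came to light, not evidence of unequal enquiry.

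It is also fair to say that an all-event count is not free of bias. Lessons on consent and on dating and relationship violence could increase disclosure, and background events dilute a signal. That is why the secondary splits are kept.

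**Conclusion.** The point holds in a limited form. The only comparison the plan states for this purpose selects events on judged relatedness before comparing arms. As written, it can show an arm difference without excess harm, and it omits excess that is not attributed to the programme. The committee's view of the events is not restricted.

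The size cannot be stated, because the documents give neither event rates nor attribution rates. The conclusion assumes the natural reading of the qualifier (if it governs SAEs only, the point applies to SAEs only) and little contamination of control schools. It is worth correcting because the events are already collected without a filter and the remedy is cheap.

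**What to change.** In *Ethical issues, safeguarding and SAEs*:

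1. State that all safeguarding concerns and SAEs are tabulated for the DMEC by arm, with numbers of students and schools as denominators, and that this is the main between-arm comparison. Supplementary Material 4 shows that such denominators exist: 24 intervention schools with 4511 students and 25 control schools with 4506 at baseline.
2. Keep judged relatedness as a secondary split and say who makes the judgement. Add route of detection (school report, survey, process-evaluation visit) as another.
3. Reword the trigger sentence so that it is clear whether the qualifier covers safeguarding concerns as well as SAEs.

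The cost is about one protocol sentence and one report table, plus a field for route of detection if it is not already recorded. Judging relatedness without sight of arm would be a further refinement, but it needs an assessor and redaction and is not required here. Delivery was due to finish by July 2024, so the same table can also serve the final safety report. The decision on stopping stays with the DMEC.
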